#### Randomization

A week before the first AB or HEP session, research assistants randomize and enroll participants via phone. Participants are randomly assigned in a 1:1 ratio to AB intervention or HEP control to ensure comparability between groups. The unblinded study biostatistician created the randomization schedule with permuted blocks of random sizes and implemented it in REDCap. Randomization is stratified according to ECD type (subjective vs mild cognitive impairment). To maintain single-arm blinding, study staff and materials refer to AB and HEP as AB1 and AB2, respectfully. Without unblinding, research assistants notify each participant about their group assignment, schedule weekly session times, and provide links to the AB or HEP websites. Research assistants review expectations for attending the group sessions, including the following: (1) timeliness, (2) quiet location, (3) respectfulness of others, (4) no multitasking, (5) wearing the watch, (6) having a pen and the manual ready, and (7) responding to daily smartphone surveys to complete home practice. The research assistant mails a printed copy of the program manual to be received by participants before the first group session. Participants in the AB arm receive a Fitbit to wear, starting after session 1 to ensure that step count assessment remains blind in both groups. Participants are considered to be enrolled after completing session 1 of the AB or HEP arms.

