### Data Analytic Plan

#### Power Analysis

Our blinded statistician used SAS (version 9.4; SAS Institute) [92] for the power analysis. Our primary outcome requires clinically important improvements in both functional measures (step count and 6-min walk test) and patient-reported outcome (Patient-Reported Outcomes Measurement Information System Physical Function). Allowing for 20% dropouts, 260 participants recruited (130/group; 104/group completing the study) would provide 92.3% power (Cronbach α=.05; 2 sided) to detect the minimum clinically important difference in step count (1000 steps) [93,94] between the AB and HEP groups in the change from baseline to postintervention assessment. This assumes an SD of 2120, which is the upper 80% confidence limit for the SD observed in our pilot study, as recommended [95]. We also assume 50% correlation between preintervention and postintervention measures. This sample size provides 81.8% power for a difference of 54 meters (the minimum clinically important difference) [96] in the 6-minute walk test (SD 135 based on our pilot data) and >99.9% power for a difference of 5.48 points (minimum clinically important difference) [97] for the Patient-Reported Outcomes Measurement Information System Physical Function score (SD 7.61 based on our pilot data). Assuming a correlation of 0.5 between significant results of step count and 6-minute walk test, the power of the study would be 80.7% (based on simulations) of having a statistically significant result for all 3 coprimary end points.

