#### Data Analyses

##### Overview

Our blinded statistician will conduct all data analyses using SAS (version 9.4) [92]. We will estimate treatment-dependent changes in primary (objective, performance-based, and patient-reported physical function) and secondary outcomes (patient-reported and objective cognitive function and emotional function). We will follow the intention-to-treat principle and include all randomized participants in our primary efficacy analyses. Data will be analyzed using a shared-baseline, linear mixed model with fully unstructured covariance among repeated measures. The shared-baseline assumption reflects the true state of the population before randomization and has the benefit of adjusting for chance differences at baseline. Linear mixed models with maximum likelihood estimation are unbiased when data are missing at random, conditional on the observed data. If loss to follow-up is strongly treatment-dependent (relative risk >2), we will use perturbed multiple imputation to assess the robustness of estimates from the primary model if data were missing in not-at-random manner.

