##### Aim 1: Efficacy of AB (Baseline to Posttest Period)

We have already established the feasibility benchmarks of the intervention and control [28,30]; therefore, emphasis of this study is on establishing the efficacy of AB*.* Accordingly, the primary analysis will compare the changes in primary and secondary outcomes (continuous measures) from baseline to posttest period between the randomized conditions. For each outcome, we will compare the effect of AB versus control on changes from baseline to the posttest period using linear contrasts. With 3 coprimary outcomes, no adjustment for multiple comparisons is needed; therefore, we will use 2-sided tests at *P*<.05 to declare the superiority of AB, maintaining an overall 5% type-1 error at our primary postintervention time point. The success of the trial will be declared if participation in AB is associated with statistically significant and clinically important improvement from baseline to posttest period over participation in control based on the 3 physical function outcomes.

We will conduct several sensitivity analyses to ensure that a conclusion about efficacy is robust to possible deviations from the assumptions of the primary model. Baseline parameters will be included to account for chance differences owing to randomization and to explain the sources of variation in response that are independent of treatment group. We will also use a Wilcoxon rank sum test comparing the change in scores between the 2 groups to avoid any parametric assumptions about the data. All secondary outcome measures will be analyzed using the same shared-baseline, linear mixed model and the same secondary sensitivity analyses. Step-down, Bonferroni-adjusted *P* values will be used to control for multiple comparisons regarding the secondary outcomes.

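### The only not-at-random sensitivity analysis runs only if the dropout relative risk exceeds 2, although bias from informative dropout can arise at any ratio, including 1

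*Protocol article*

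**What the plan says.** The Overview under Data Analyses in the protocol article sets the analysis population: "We will follow the intention-to-treat principle and include all randomized participants in our primary efficacy analyses". It justifies the shared-baseline mixed model with the statement "Linear mixed models with maximum likelihood estimation are unbiased when data are missing at random, conditional on the observed data". It then gives one route for departures from that assumption: "If loss to follow-up is strongly treatment-dependent (relative risk >2), we will use perturbed multiple imputation to assess the robustness of estimates".

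The Aim 1 section adds two sensitivity analyses that carry no condition: inclusion of baseline covariates, and a Wilcoxon rank sum test on change scores. The same section declares success only if AB's improvement over control is both statistically significant and clinically important on the three physical function outcomes.

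The Power Analysis section gives the dropout allowance: "Allowing for 20% dropouts, 260 participants recruited (130/group; 104/group completing the study) would provide 92.3% power". The Results section reports two losses among 37 enrolled participants, one in each arm.

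**The concern.** Whether missing at random holds depends on why participants leave and what their unobserved outcomes would have been. The ratio of dropout rates measures neither. The arms make different demands: AB sets step goals that rise when they are met, while HEP is education only. Reasons for leaving could therefore differ between arms even when the rates are equal.

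The two unconditional sensitivity analyses do not fill the gap. Covariate adjustment still assumes missing at random, although it may make that assumption more plausible. The Wilcoxon test concerns the shape of the distribution and uses only participants with an observed change score. If the trigger stays off, the stated plan contains no check on the one missing-data assumption it names. What is at stake is a claim of significant and clinically important benefit in all randomised participants.

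**Working it through.** **Inputs from the protocol article.** Power Analysis: 130 randomised and 104 completing per group; step-count SD 2120, pre-post correlation 0.5, minimum clinically important difference (MCID) 1000 steps; 6-minute walk SD 135 m, MCID 54 m; PROMIS Physical Function SD 7.61, MCID 5.48. Randomization: 1:1. Aim 1: two-sided 5% tests. Data Analyses, Overview: trigger at relative risk (RR) above 2.

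**Reproducing the plan's own figure.** SD of change = 2120 × √(2 × (1 − 0.5)) = 2120. SE = 2120 × √(2/104) = 294 steps. With 206 degrees of freedom, the noncentral t gives 92.3% power for 1000 steps, as stated. The same method gives 81.9% for the 6-minute walk (stated 81.8%). The inputs are therefore read as the plan intends.

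**How often the trigger fires.** Set the average of the two dropout rates at 20%, so the lower rate is 0.40/(1 + RR) and the higher is RR times that. Losses in each arm are binomial with n = 130. The trigger fires when the larger count exceeds twice the smaller. The plan does not state a direction, so both are counted.

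| True RR | Dropout rates | P(trigger fires) |
|---|---|---|
| 1.0 | 20.0% and 20.0% | 0.7% |
| 1.25 | 22.2% and 17.8% | 3.4% |
| 1.5 | 24.0% and 16.0% | 12.9% |
| 1.75 | 25.5% and 14.5% | 29.4% |
| 2.0 | 26.7% and 13.3% | 48.5% |

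With 52 losses in all (20% of 260), the first split that fires is 35 against 17. A split of 34 against 18 (26.2% and 13.8%; RR = 34/18 = 1.89; chi-square P=.013) does not.

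**Bias in the contrast.** Let p be the share lost in an arm and δ the amount by which its dropouts fall short of their missing-at-random prediction. The model then overstates the AB effect by

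p_AB × δ_AB − p_HEP × δ_HEP.

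The documents give no δ, so the following values are assumptions. Results are for step count.

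| p_AB, p_HEP | δ_AB, δ_HEP | Overstatement |
|---|---|---|
| 20%, 20% | 1000, 0 | 0.20 × 1000 = 200 |
| 20%, 20% | 2120 (one SD), 0 | 0.20 × 2120 = 424 |
| 20%, 20% | 1000, −1000 | 200 + 200 = 400 |
| 20%, 20% | 1000, 1000 | 200 − 200 = 0 |
| 26.2%, 13.8% | 1000, 0 | 34/130 × 1000 = 262 |
| 5%, 5% | 1000, 0 | 0.05 × 1000 = 50 |

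None of these dropout rates has an RR above 2. In the first row a model estimate of 1000 corresponds to a true 800. The excess is 20% of the MCID, or 200/800 = 25% of the true effect. The matching case for the 6-minute walk is 54 − 0.20 × 54 = 43.2 m.

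**Tipping points.** Take equal 20% dropout, a shift in AB only, an observed effect equal to the MCID, and the SE held at its 104-per-arm value. The tipping shift is (observed effect − t × SE)/0.20, with t × SE the smallest significant difference.

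- Step count: (1000 − 580)/0.20 ≈ 2100 steps
- 6-minute walk: SE = 135 × √(2/104) = 18.7 m, so (54 − 36.9)/0.20 ≈ 85 m, or 0.63 SD
- PROMIS Physical Function: SE = 7.61 × √(2/104) = 1.06, so (5.48 − 2.08)/0.20 ≈ 17 points

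All three lie beyond the MCID.

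**The case against.** Several points on the other side have force.

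- **The 20% is an allowance, not a forecast.** The only observed figure is 2 of 37, with one loss per arm (1/18 against 1/19, RR about 1.06). If loss stays near 5%, the illustrated bias is about 50 steps. At that level the trigger also fires more often by chance, about 20% of the time at a true RR of 1. A reader might infer that the problem goes unchecked in most plausible scenarios. The documents do not support that, because the early data point to a smaller problem. They are early data, however, with enrollment planned until March 2026.
- **Imbalance is not irrelevant.** The dropout rates enter the bias formula directly, and equal rates with equal departures give zero bias. The trigger is incomplete rather than beside the point.
- **Significance is fairly robust.** With an observed effect equal to the MCID and 20% lost per arm, an AB-only shift of a full MCID leaves all three outcomes significant. A reader might infer that the rule puts a false-positive finding within easy reach. The plan's figures do not show that. The added requirement of clinical importance, or a smaller observed effect, is more exposed.
- **The condition is prespecified.** It has a numeric threshold and governs a sensitivity analysis only, so it does not inflate the type I error of the primary test. Nor does the rule forbid running the analysis in other cases.

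The details of the shifts may properly sit in an analysis plan that is not shown. The trigger is stated in the article, and it can be judged as written.

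**Conclusion.** The point holds for the trigger. The article commits to its only not-at-random analysis when the dropout RR exceeds 2, and that criterion can miss bias of practical size. At the 20% allowance the analysis is more likely than not to be omitted for any true RR up to 2. These probabilities assume independent binomial losses with 130 per arm.

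The 200-step figure is an illustration. It assumes 20% loss in each arm and a departure in AB dropouts alone, and it falls to about 50 steps at 5% loss. It matters most for the clinical-importance part of the success rule: if that part is judged by comparing the estimate with the MCID, which the article does not spell out, a reported 1000 steps would meet it when the true effect is 800. The calculations do not show that the trial's conclusion would be wrong. They show that the stated plan may leave it untested.

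**What to change.** Delete the RR>2 condition in the Overview under Data Analyses. State that perturbed multiple imputation will be run for all three coprimary outcomes whatever the dropout balance. Let the shift applied to imputed values differ between arms. Extend it until significance is lost or the shift becomes implausible, and report that tipping point. The range should not stop at the MCID, since with the plan's inputs and an observed effect equal to the MCID the tipping point lies beyond it for every coprimary outcome. It would also help to report the shift at which each estimate falls below its MCID, because the success rule requires clinical importance.

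The cost is a little more analysis work with a method the plan already names. Sample size, power and trial conduct do not change.

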##### Aim 1: Efficacy of AB (Baseline to Posttest Period)

We have already established the feasibility benchmarks of the intervention and control [28,30]; therefore, emphasis of this study is on establishing the efficacy of AB*.* Accordingly, the primary analysis will compare the changes in primary and secondary outcomes (continuous measures) from baseline to posttest period between the randomized conditions. For each outcome, we will compare the effect of AB versus control on changes from baseline to the posttest period using linear contrasts. With 3 coprimary outcomes, no adjustment for multiple comparisons is needed; therefore, we will use 2-sided tests at *P*<.05 to declare the superiority of AB, maintaining an overall 5% type-1 error at our primary postintervention time point. The success of the trial will be declared if participation in AB is associated with statistically significant and clinically important improvement from baseline to posttest period over participation in control based on the 3 physical function outcomes.

We will conduct several sensitivity analyses to ensure that a conclusion about efficacy is robust to possible deviations from the assumptions of the primary model. Baseline parameters will be included to account for chance differences owing to randomization and to explain the sources of variation in response that are independent of treatment group. We will also use a Wilcoxon rank sum test comparing the change in scores between the 2 groups to avoid any parametric assumptions about the data. All secondary outcome measures will be analyzed using the same shared-baseline, linear mixed model and the same secondary sensitivity analyses. Step-down, Bonferroni-adjusted *P* values will be used to control for multiple comparisons regarding the secondary outcomes.

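### The only nonparametric sensitivity check uses raw change scores while the primary model adjusts for baseline, so a disagreement could not be put down to non-normality; a baseline-adjusted rank test would do the job better at almost no cost.

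*Protocol article*

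**What the plan says.** Data Analyses, Overview, sets the primary analysis: "Data will be analyzed using a shared-baseline, linear mixed model with fully unstructured covariance among repeated measures". The same section gives as a merit of the shared baseline that it "has the benefit of adjusting for chance differences at baseline".

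Aim 1 then lists sensitivity analyses meant to show that the efficacy conclusion survives departures from the primary model's assumptions. One is parametric: "Baseline parameters will be included to account for chance differences owing to randomization". The other is the only nonparametric one: "We will also use a Wilcoxon rank sum test comparing the change in scores between the 2 groups". Its stated purpose is to do without parametric assumptions. No baseline covariate or stratum is named for it. The same sensitivity analyses are to be applied to all secondary outcomes.

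The Power Analysis section supplies the planning correlation: "We also assume 50% correlation between preintervention and postintervention measures".

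**The concern.** A robustness check is most informative when it relaxes one assumption and leaves the rest of the analysis as it was. This one changes two things. It replaces a normal-theory test with ranks, and it replaces baseline adjustment with a simple change score, which fixes the slope on baseline at 1. If the Wilcoxon result is weaker than the primary result, the reader cannot tell whether the data are non-normal or whether the check is simply less efficient.

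At stake is how the results will read. With three coprimary outcomes that must all succeed, there are three chances for a less efficient check to appear to contradict a correct finding.

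**Working it through.** **Inputs from the Power Analysis section.** 104 completers per arm; two-sided 5% tests; differences and SDs of 1000/2120 (steps), 54/135 (6-minute walk) and 5.48/7.61 (PROMIS Physical Function); pre-post correlation ρ = 0.5. The plan states ρ directly after the step-count SD; using it for the other two outcomes is an inference, which the reproduction below supports.

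**Step 1: reproduce the plan's power.** The variance of a change score is 2(1 − ρ)σ² = 2(1 − 0.5)σ² = 1.00σ², so the SD of change equals the stated SD. The noncentrality is δ / (SD·√(2/104)):

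- Steps: 1000 / (2120 × 0.1387) = 3.40, power 92.3% (stated 92.3%).
- 6-minute walk: 54 / (135 × 0.1387) = 2.88, power 81.9% (stated 81.8%).
- PROMIS: 5.48 / (7.61 × 0.1387) = 5.19, power 99.9% (stated >99.9%).
- Steps and walk jointly, with correlation 0.5 between the two significance results: 0.923 × 0.818 + 0.5·√(0.923 × 0.077 × 0.818 × 0.182) = 80.6% (stated 80.7% for all three; PROMIS costs almost nothing).

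The stated power is thus power for an unadjusted change-score test.

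**Step 2: what baseline adjustment adds.** The residual variance after adjustment is (1 − ρ²)σ² = 0.75σ². Power becomes 97.4% for steps and 91.2% for the 6-minute walk. Wilcoxon on change gives about 91% and 80%. Rank analysis of covariance gives about 96% and 90%.

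**Step 3: all three outcomes, by simulation.** Normal data, ρ = 0.5, complete cases, analysis of covariance standing in for the shared-baseline model, 30,000 trials per row. The correlation between outcomes is an assumption. The adjusted rank test here is a rank sum test on baseline-adjusted residuals. A miss means non-significance on at least one outcome when the adjusted analysis is significant on all three.

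| Correlation between outcomes | Joint power: adjusted | Wilcoxon on change | Adjusted rank test | Missed by Wilcoxon | Missed by change-score t-test | Missed by adjusted rank test |
|---|---|---|---|---|---|---|
| 0 | 88.3% | 72.5% | 86.5% | 19.7% | 16.6% | 3.5% |
| 0.3 | 89.4% | 74.6% | 87.5% | 17.9% | 15.4% | 3.2% |
| 0.5 | 89.4% | 75.8% | 88.1% | 16.7% | 14.2% | 2.7% |
| 0.8 | 90.3% | 78.3% | 88.9% | 14.8% | 12.6% | 2.6% |

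An outcome correlation of about 0.8 to 0.85 matches the plan's 0.5 between significance results, so the plan's own assumption sits at the one-in-seven end. A separate simulation of rank analysis of covariance on ranks of both measures gave misses of 4-5%.

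The change-score t-test column locates the loss. It involves no ranking, yet accounts for most of the misses; ranking adds only 2 to 3 points.

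**Step 4: sensitivity of the miss rate.**

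- Pre-post correlation (between-outcome correlation 0.5): about 32% at ρ = 0.3, 24.5% at 0.4, 9.7% at 0.6 and 3.6% at 0.7.
- Heavy tails (assumed shapes, ρ = 0.5): about 10% with t(5) and about 4% with t(3). With t(3), Wilcoxon's joint power (94-95%) exceeds that of the adjusted parametric analysis (88-89%). Rank analysis of covariance stayed ahead of Wilcoxon on change in both cases and at ρ = 0.7.
- Success also requiring each point estimate to reach its minimum clinically important difference: 1-2% at ρ = 0.5.

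**The case against.** The strongest reply is that nothing turns on this test. It is one of several sensitivity analyses, success is declared from the primary model, and no rule requires the Wilcoxon P value to fall below .05. It is valid under randomization, with no bias and no inflation of type I error. That stands. A reader might infer that the check would overturn one in five or six genuine trial successes. The documents do not support this, because the test has no pass/fail role, and because the success rule asks for clinical importance as well as significance. If clinical importance means a point estimate at or above the minimum clinically important difference, the miss rate is only 1-2%. The article does not say how it is judged. On that reading, though, only 12-35% of simulated trials succeed at the planned effects, whereas the 80.7% joint power is for significance alone.

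It is also fair that the largest miss rates come from normal data, where the check is least needed, and that the gap narrows under heavy tails. Against the change-score basis on which the trial was sized, Wilcoxon misses only about 4-7%. But the analysis it is meant to check is the baseline-adjusted one. The other sensitivity analysis does add baseline parameters, but it is parametric and so does not fill the gap.

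A second tempting reading is that leaving ECD type out of the Wilcoxon test is a further discrepancy, since "Randomization is stratified according to ECD type (subjective vs mild cognitive impairment"). The primary model is not stated to include ECD type either, so this is no difference between the two analyses, and the article gives no figure from which to size it. The point rests on baseline adjustment alone.

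**Conclusion.** The point holds as a modest improvement to a supportive analysis. The check differs from the primary model in its use of baseline as well as in its distributional assumption, and most of the disagreement to be expected at the planned effects comes from the former. Under normal data and ρ = 0.5 for all outcomes, it would be non-significant on at least one coprimary in roughly 15-20% of trials significant on all three, against about 3-5% for a baseline-adjusted rank test. These figures rest on complete cases, on analysis of covariance as a stand-in for the mixed model, and on an assumed between-outcome correlation of 0 to 0.8. They depend strongly on ρ. The validity of the trial and its declared result are unaffected.

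**What to change.** In the Aim 1 section, replace the Wilcoxon test on change scores with Quade's rank analysis of covariance, for the coprimary and the secondary outcomes. Rank the posttest and baseline values, regress posttest ranks on baseline ranks, and compare the residuals between arms. The test needs no normality assumption, and randomization justifies it because the baseline distributions are the same in both arms. Stratifying the comparison by ECD type is optional. The Wilcoxon test on change may be kept as a descriptive companion.

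The cost is one sentence in the plan and a few lines of SAS, using data already collected. The downside is a slightly less familiar test. The change should be fixed before unblinding.
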